### Plans to give access to the full protocol, participant-level data, and statistical code {31c}

Upon publication of the main trial results, the full protocol will be publicly accessible. Participant-level data will remain pseudonymized and confidential, in compliance with privacy and data protection regulations. However, de-identified datasets suitable for secondary analysis may be shared via Dataverse, subject to ethical approval and data protection standards. The statistical code used in the analysis will be available upon request, subject to ethical review and compliance with data protection standards.

## Oversight and monitoring

### Composition of the coordinating center and trial steering committee {5d}

The coordinating center (Tranzo, Tilburg University) oversees overall study management and administration. Day-to-day trial operations (screening, recruitment, scheduling, data capture, and protocol adherence) are handled by the Trial Management Group (TMG: principal investigator [chair], trial coordinator, data manager, lead trainer, and site leads).

A Trial Steering Committee (TSC) provides strategic oversight and independent advice. Membership: principal investigator (chair), co-investigators not involved in daily operations, an independent senior researcher from Tilburg University (not otherwise involved in the trial), the trial statistician, and site representatives from participating services. A PPI advisor (lived experience of MID/substance use) may attend selected meetings to advise on participant-facing materials; they are non-voting and not involved in safety adjudication.

Meeting cadence: the TMG meets monthly; the TSC meets quarterly (or ad hoc in response to safety signals). The TSC reviews recruitment and retention, protocol adherence, data quality summaries, adverse event reports, and any proposed protocol amendments, and escalates material issues to the Ethics Review Board.

#### Risk measures and mitigation strategies

To ensure the trial’s integrity and participant safety, potential risks and corresponding mitigation strategies have been identified in Table 4. These measures address anticipated challenges, including dropout rates, adverse events, and data security, ensuring that risks are actively monitored and mitigated throughout the study.

**Table 4 Tab4:** Risk measures

Risk	Likelihood	Impact	Mitigating measures
Higher dropout rate	Medium	Reduced sample size	Flexible scheduling, involvement of helpers, regular check-ins, providing rewards
Adverse events (e.g., distress)	Low-medium	Emotional discomfort or dropout	Clear protocols, trained trainers, support from care teams
Limited understanding	Low	Incomplete or skewed data	Adapted materials, visual aids, helper involvement
Privacy or data breaches	Low	Loss of trust or ethical violations	Data security, pseudonymization, GDPR compliance
Emotional burden of reflection	Medium	Emotional strain or disengagement	Supportive approaches like MI and CBT, structured breaks, empathetic facilitation

### Composition of the data monitoring committee, its role, and reporting structure {21a}

No independent Data Monitoring Committee (DMC) is convened for this study. Given the open-label, behavioral, non-invasive nature of the intervention and its classification as posing no more than minimal physical risk, a full DMC would be disproportionate. Instead, safety and data quality are overseen through a two-layer structure:

Internal monitoring (trial team).The Principal Investigator (PI) oversees routine safety and quality checks after each assessment wave (T2/T3/T4). The trial team monitors data entry, protocol adherence, retention, and protocol deviations. A priori pause/stop criteria are defined (see Harms {22}).Independent safety auditing.Proportionate independent oversight is provided by an Independent Safety Auditor (ISA)—a senior researcher at Tilburg University who is not involved in trial design, recruitment, intervention delivery, data collection, randomization, or statistical analysis, and is not in the PI’s line management. The ISA is appointed before first enrolment; their identity and contact details are recorded in the Trial Master File and are available to the Ethics Review Board (ERB) upon request. Cadence: quarterly audits (or after ~25% of inclusions, whichever comes first). Access/scope: the ISA may access unblinded safety data (not efficacy) when required to assess relatedness/expectedness; source verification is done on site with pseudonymized records where feasible.

Checklist:Presence/completeness of informed-consent and eligibility documentation;Inclusion pace and dropout/retention;Completeness/consistency of research data;Protocol deviations and corrective actions;AEs and SAEs logs and reporting timelines.

#### Reporting structure

ISA audit memos are sent to the PI and archived in the Trial Master File; key safety findings are summarized to the sponsor and the ERB at least annually or ad hoc if a safety signal emerges. SAEs are reported to the ERB within 24 h. If predefined thresholds are crossed (e.g., ≥ 2 related SAEs or unexpected moderate-to-severe distress in > 10% of participants), the PI will pause recruitment, request an ERB review, and implement protocol modifications as needed.

#### Scope

No interim efficacy analyses are planned; oversight focuses on participant safety and data integrity. This monitoring plan is proportionate to the trial’s risk profile and complies with ERB oversight requirements (see also Harms {22} for definitions, ascertainment, and reporting).

### Adverse event reporting and harms {22}

Adverse events will be closely monitored throughout the study. Harms are defined as any adverse psychological, behavioral, or medical event related to participation, including (but not limited to) increased distress, relapse episodes, psychiatric crisis requiring intervention, or hospitalization.

All reported or observed adverse events will be documented in detail (event, onset/offset, severity, relatedness, expectedness, action taken, outcome), including an assessment of severity and potential relationship to the intervention by the primary researcher. Ascertainment will occur during each study contact (T2, T3, T4) via participant self-report and facilitator observation, with additional spontaneous reporting allowed at any time; relevant chart information will be reviewed where applicable. SAEs will be reported to the Ethics Review Board within 24 h. If necessary, protocol modifications will be implemented promptly to ensure participant safety.

### Frequency and plans for auditing {23}

Proportionate internal auditing will occur after the first 10 inclusions and then quarterly (or ~10% file sampling, whichever comes first). Independent ISA audits are conducted on the same cadence (or at ~25% inclusion intervals) using a predefined checklist. Audit memos are sent to the PI and archived in the Trial Master File; key safety findings are summarized to the sponsor and the ERB at least annually or ad hoc if a safety signal emerges. Pause/stop criteria are prespecified (see Harms {22}); SAEs are reported to the ERB within 24 h.

### Plans for communicating important protocol changes to relevant parties {25}

Any amendments to the protocol, such as changes in eligibility criteria or outcome measures, will be communicated to relevant stakeholders, including the ethics committee. These amendments will also be documented in the trial registry and disseminated via appropriate scientific channels, such as peer-reviewed journals, conference presentations, and research networks, to maintain transparency. Direct communication of protocol changes to participants will not be undertaken.

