### Who will obtain informed consent? {26a}

Recruitment will be conducted jointly by researchers from Tilburg University and care professionals at the participating organizations: care professionals identify and pre-screen eligible clients and introduce the study; Tilburg University researchers then confirm eligibility, provide standardized information in accessible formats, and obtain written informed consent. Researchers from Tilburg University with expertise in intellectual disabilities and substance abuse will be responsible for obtaining informed consent. They will ensure that all participants, or their legal representatives where applicable, fully understand the nature of the study, the intervention, and any potential risks or benefits. This process will be guided by the Zelen design, which facilitates ethical and transparent participant engagement.

Participants randomized to the intervention group (Beat the Kick) will be approached after randomization. Researchers will provide a detailed explanation of the intervention and study procedures, seeking their consent to participate in both the intervention and the study assessments, such as questionnaires and interviews. Participants randomized to the CAU group will be informed of their allocation and asked to consent to participate in the study assessments only, which are essential for evaluating study outcomes but do not involve active participation in the intervention. The primary goal is to seek consent directly from participants whenever possible. In cases where a legal representative is required, formal consent will also be obtained from the representative, in compliance with Dutch law and ethical guidelines. Consent from both the participant and their representative will be required, as the participant’s engagement is crucial for a motivation-based intervention. Researchers will use tailored communication strategies, including clear language and visual aids, to address any questions or concerns and ensure participants’ comprehension of the study details.

All questionnaires will be completed digitally or on paper, with assistance from the researcher if needed, ensuring accessibility and efficiency in data collection. Model versions of the participant information sheet and consent form for both study groups are provided as supplementary materials (Additional files 1 and 2).

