### Criteria for discontinuing or modifying allocated interventions {11b}

Participants may discontinue the intervention for various reasons. They are free to withdraw from the study at any time without providing an explanation, and their autonomy in making this decision will be fully respected. If a participant’s condition deteriorates, for example due to increased substance use, the onset of severe psychiatric symptoms, or emerging safety concerns, healthcare professionals may advise discontinuation of the intervention in order to safeguard the participant’s well-being.

Discontinuation may also be considered if the participant experiences substantial emotional distress or other adverse effects that appear to be directly related to the intervention. In situations where participants consistently miss sessions or have difficulty engaging with the intervention, additional support will be offered to promote continued involvement. Whenever possible, modifications will be made in collaboration with the participant and their caregiver to enhance engagement, rather than opting for discontinuation. All forms of discontinuation, including partial disengagement such as repeated absences or reduced participation, will be documented and may be analyzed as outcomes in their own right. These instances may provide valuable insight into motivational dynamics or barriers to sustained participation.

If a participant voluntarily initiates formal addiction treatment during the study period, this will be recorded as a meaningful outcome rather than treated as a reason for discontinuation. This step will be interpreted as an indication of increased autonomous motivation to change, provided the decision to seek treatment is made voluntarily and not due to external pressure.

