### Participant timeline {13}

Participants will be enrolled in the study following a thorough screening and informed consent process. The intervention period will last 10 weeks, during which participants will receive either the Beat the Kick intervention or CAU support. Assessments will be conducted at four key time points: pre-treatment (T1), post-treatment (T2), and during follow-ups at 1 month (T3) and 6 months (T4). This structured timeline ensures a comprehensive evaluation of both the immediate and long-term effects of the intervention. A schematic diagram of participant flow is presented in Fig. 2, and the detailed schedule of enrolment, interventions, and assessments is shown in Fig. 3.

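### The amendment rule bars direct notice to participants without exception, although the protocol foresees changes made because of harm while enrolled people continue

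*Protocol article*

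**What the plan says.** Four parts of the protocol article bear on this point.

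- **Plans for communicating important protocol changes {25}.** The scope is every amendment: "Any amendments to the protocol, such as changes in eligibility criteria or outcome measures, will be communicated to relevant stakeholders, including the ethics committee". Eligibility and outcome measures are only examples. The registry and scientific channels are also named as outlets. The section closes: "Direct communication of protocol changes to participants will not be undertaken".
- **Adverse event reporting and harms {22}.** Changes made because of harm are expected: "If necessary, protocol modifications will be implemented promptly to ensure participant safety".
- **Reporting structure, under the data monitoring section {21a}.** If thresholds are crossed (for example, two or more related serious adverse events, or unexpected moderate-to-severe distress in more than 10% of participants), "the PI will pause recruitment, request an ERB review, and implement protocol modifications as needed".
- **Who will obtain informed consent? {26a}.** Researchers are to ensure that participants, or their legal representatives where applicable, "fully understand the nature of the study, the intervention, and any potential risks or benefits".

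On withdrawal, the section on discontinuation {11b} says of participants: "They are free to withdraw from the study at any time without providing an explanation".

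**The concern.** Consent in this trial rests on participants understanding the risks, and the right to withdraw is useful only to someone who knows of a reason to use it. The protocol accepts that the known risks may change during the trial and that the protocol may be modified in response. Its rule on amendments then excludes direct notice to the people exposed to that risk, with no carve-out for safety.

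Participants are adults with mild intellectual disability or borderline intellectual functioning, some of whom need a legal representative's consent alongside their own. The outlets the section names (ethics committee, registry, journals, conferences, research networks) are not designed to reach them. What is at stake is participant protection and continuing consent, not the trial's inference.

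**Working it through.** No formula applies, and the article gives no figure to reproduce. The check sets the sections side by side.

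1. **Does the rule cover safety changes?** Yes. Section {25} opens with any amendment, and its last sentence speaks of protocol changes without qualification. This is the current text of version 1.0, not a record of superseded wording.

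2. **Does the protocol expect changes made because of harm?** Yes, twice: in the harms section {22} and under Reporting structure.

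3. **Are people still in the trial when such a change is made?** Yes. Crossing a threshold pauses recruitment. The article does not say that sessions or follow-up pause for those already enrolled. On time in the trial, Participant timeline {13} states: "The intervention period will last 10 weeks". Trial design {8} adds assessments at 1 and 6 months after the intervention. Enrolled people would therefore continue under the changed protocol.

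4. **Does any other section supply an exception or another route?** The candidates do not:
   - Discontinuation {11b} provides for modifications agreed with the participant and caregiver. These are individual adaptations to sustain engagement, not amendments.
   - Post-trial care {30} offers support to people already distressed by the intervention. It does not inform others of a new risk.
   - Retention {18b} limits assessment reminders to the data collection schedule.
   - Interim analyses {21b} concerns early termination of the trial.
   - The Independent Safety Auditor's checklist {21a} covers consent documentation, but the article does not require updated information or renewed consent.
   - Dissemination {31a} sends participants a results summary after the primary analysis.

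5. **Is this an omission that a fuller document might fill?** No. It is an explicit statement. A fuller document could contradict it but could not complete it.

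Taken together, section {25} conflicts with the consent aim in {26a} in exactly the situation that {22} and Reporting structure describe.

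**The case against.** The strongest reply is that the sentence is narrower than it looks and that other safeguards exist. Much of this stands and limits how far the point can go.

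- **Only direct communication is excluded.** The list of relevant stakeholders is open, so word could reach a participant through staff or a representative. A reader might infer that participants could never learn of a change. The text supports only that they would not be told directly under the plan, and that no other route is set out.
- **Representatives are not excluded.** A reader might infer that legal representatives are shut out too. Section {25} names participants only, and representatives may fall within relevant stakeholders.
- **Harm ascertainment does not depend on notice.** A reader might infer that uninformed participants could not report a newly recognised symptom. Outcomes {12} provides structured checklists and open queries at T2, T3 and T4. The harms section {22} adds self-report, facilitator observation, spontaneous reporting and chart review. None of these requires the participant to know of an amendment.
- **A headcount is not well founded.** One might multiply 138 recruits over 52 weeks by about 36 weeks in the trial (10 weeks plus roughly 26): 138/52 × 36 ≈ 95 people affected at once. That assumes uniform accrual, which the article does not state, and a rate above the projected pool of about 120 a year in Study setting {9}. At 120 a year the same sum is 120/52 × 36 ≈ 83. Both figures include care-as-usual participants, who do not receive the programme, and both matter only if such an amendment occurs.
- **Other protections apply.** Crossing a threshold triggers ethics review, and the board could require notification. Professionals may advise an individual to discontinue. The programme is described as non-invasive and of no more than minimal physical risk. The information sheets (Additional files 1 and 2) are not available here and may deal with new information.

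What remains is that none of these safeguards tells a participant about a changed risk. An ethics board's requirement or a consent form that promised notice would contradict section {25} rather than make it sound.

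**Conclusion.** The point holds in limited form. The protocol states, for any amendment and without exception, that participants will not be told directly. It also foresees modifications made because of harm while enrolled people continue, and it bases consent on understanding risk. These sections must be reconciled.

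The size is conditional. The rule has effect only if an amendment touching risk, procedures or burden is made, and the article gives no basis for a probability or a count of people affected. Sample size, power, error rates, randomisation and analysis do not change. The correction is worthwhile and easy, but its importance is moderate rather than critical. The conclusion rests on the article's wording alone and assumes that the information sheets do not set a contrary rule.

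**What to change.** Replace the last sentence of section {25} with a rule along these lines:

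- Changes that affect participants' risk, procedures or burden, including any modification that follows a crossed safety threshold, are communicated in accessible format to affected participants still in the intervention or follow-up and, where applicable, to their legal representatives.
- Continued consent is confirmed and documented.
- Purely administrative changes are exempt.

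The Independent Safety Auditor already checks consent documentation, so compliance can be verified under that existing item. A cross-reference from the harms section {22} and Reporting structure would make the sections consistent, and the information sheets should be checked for agreement.

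The cost is a short amendment now and, if the rule is ever triggered, a brief notice and consent confirmation. A few participants may withdraw once informed, which is a consequence of continuing consent and should be accepted.

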### Dissemination plans {31a}

Study results will be disseminated via peer-reviewed publications, conference presentations, and reports on organizational websites. Participants will receive a plain-language summary and infographic within 6 months after completion of the primary endpoint analysis; these materials will also be shared via AWVB channels and social media. Co-created short videos with experts by experience will enhance accessibility. To support knowledge transfer, findings will be integrated into MBO/HBO curricula through guest lectures, workshops, and case studies on motivation and substance use in MID. Results will be reported irrespective of direction or significance. A concise summary will be posted to the trial registry record in line with registry policy.

## Discussion

Substance abuse is a significant issue among individuals with MID, impacting their physical health, autonomy, and motivation for treatment [1, 2, 14]. Autonomous motivation is critical to the success of substance abuse interventions, but remains underexplored in this population. The Beat the Kick intervention was developed to fill this gap by fostering intrinsic motivation through a structured program that targets psychological needs and self-regulation [21, 26, 33]. By addressing low autonomous motivation—a key modifiable barrier to care—this intervention aims to increase treatment engagement and improve outcomes in a group that is often excluded from or underserved by mainstream addiction services [6–8].

This RCT compares Beat the Kick to CAU, evaluating its effectiveness in enhancing motivation for change and stimulating treatment engagement. A major strength of the study lies in its robust design, including individual-level randomization through a Zelen design [37], the use of validated instruments such as the TSRQ [21, 26] and the BPNSFS-ID [34], and comprehensive follow-up assessments.

Previous studies have shown that individuals with MID frequently experience low levels of treatment readiness, due to factors such as poor insight into their substance use, limited verbal skills, and challenges in expressing personal goals [10, 11]. These factors not only limit engagement but also contribute to exclusion from traditional addiction services [6, 9]. The current study builds on prior work demonstrating that motivation is a key predictor of treatment adherence and success across populations [12], and that supporting autonomy, competence, and relatedness enhances this motivation in people with intellectual disabilities [13, 26].

The structure and content of Beat the Kick incorporate several of these principles. The intervention integrates techniques from motivational interviewing and cognitive-behavioral therapy, adapted for individuals with MID through simplified language, visual support, and personalization [13, 16–18, 21]. The inclusion of trusted caregivers and the focus on real-life examples are consistent with calls for concrete, individualized approaches that acknowledge the cognitive and communicative characteristics of this population [11, 19].

Importantly, the focus on pre-treatment motivation reflects growing recognition that many individuals with MID and substance abuse issues fall into a treatment gap—not yet motivated or eligible for intensive addiction treatment, yet clearly in need of support [8, 27]. Previous research on the earlier version of Beat the Kick showed promising outcomes using a single-case experimental design [21], but generalizability remained limited. The current RCT responds to this limitation by testing the intervention across six care organizations, enhancing external validity.

Nonetheless, several limitations must be considered. Due to the nature of the intervention, neither participants nor facilitators could be blinded to group assignment, which increases the risk of performance bias [37]. Additionally, reliance on self-report measures for substance use and psychological needs may introduce social desirability bias—particularly relevant in MID populations, who are known to provide socially desirable answers [13]. However, the instruments used in this study have been validated in this population and were supported with visual aids to facilitate comprehension and reduce misunderstanding [23, 35, 39].

Another important consideration concerns participant dropout, which is a known challenge in studies involving individuals with co-occurring MID and substance abuse problems [1, 10, 28]. Despite proactive strategies to support retention—such as flexible scheduling and involvement of caregivers—a certain level of dropout is expected. Beyond its quantitative impact on statistical power, dropout may also introduce systematic bias, particularly if individuals who discontinue differ meaningfully from those who remain in the study. For instance, participants with lower verbal ability, greater psychological distress, or more unstable living conditions may be more likely to disengage, thereby skewing the sample towards individuals with more stable or supportive environments.

To better understand this dynamic, the study will qualitatively document reasons for discontinuation, capturing both participant-reported factors (e.g., emotional burden, lack of perceived relevance) and contextual elements (e.g., caregiver availability, competing life stressors). This information will not only support transparency in reporting but also inform interpretations of the intervention’s reach and generalizability. Furthermore, identifying patterns among dropouts may help illuminate barriers that future adaptations of the intervention need to address. In this sense, dropout is not merely a methodological limitation but also a source of insight into motivational and contextual vulnerabilities within the target population.

While the current study compares the intervention to standard care, future research may benefit from including an active control group to further isolate mechanisms of change. Moreover, adaptations of Beat the Kick could be explored for people with more severe disabilities or psychiatric comorbidities, such as those with more profound cognitive impairments or complex trauma histories [11, 15, 22].

By focusing on intrinsic motivation and supporting basic psychological needs, this study contributes to a growing body of evidence suggesting that motivation is not only a predictor of outcomes, but also a key starting point in treatment for people with MID and substance abuse problems [12, 13, 26]. If proven effective, Beat the Kick has the potential to fill a critical gap in addiction care, offering a low-threshold, evidence-based approach that can be implemented within a wide range of intellectual disability services.

